**Figure 3 figure3:**
[figure not shown]
Study design.

### Randomization

In accordance with the guidelines of Good Epidemiologic Practice, randomization is externally and centrally performed via computer by a statistician from the University of Gießen, Germany, on the class level within each school (group allocation is 1:1), which is the strongest method according to the recent Cochrane Analysis [19,33]. Different educational levels within 1 school grade are used for stratification.

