### Outcomes

The primary end point is the difference of the change in smoking prevalence in the intervention group versus the difference in the control group at 12 months of follow-up. The same longitudinal prevalence effects are studied on our females exclusively as a secondary outcome because our photoaging intervention is suspected to be more successful in females [41]. As our sample size is quite small, the secondary outcome criteria is met if 20% fewer females start smoking in the intervention group during the study period of 1 year. The differences in smoking behavior (smoking onset, quitting) between the 2 groups will be studied as additional secondary outcomes with a positive 20% difference in change of behavior set as met outcome criteria. A smoker is defined as a pupil who claims to smoke at least once in the past 30 days within the survey.

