### Analysis

To examine baseline differences we will use chi-square tests (categorical variables) and *t* tests (continuous variables). The effects of predictors (gender, culture, and social characteristics) on smoking behavior after 12 months (t3) will be calculated by robust panel logistic regression analysis. The significance level is 5% for *t* tests (double-sided) and 95% for confidence intervals (double-sided). Statistical analysis (intention-to-treat) will be performed using SPSS Statistics version 23 (IBM Corp) and STATA 14 (StataCorp LLC). In our sample, the group allocation is not on the individual level but on the class level. In order to take into account this clustering statistically we will use robust panel logistic regression (xtlogit procedure with vce [cluster] option). This procedure is also used to calculate the difference from t1 to t3 of the smoking prevalence in the control group versus the difference from t1 to t3 in the intervention group (our primary end point) by the help of STATA 14.

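### The primary analysis is a valid but inefficient change-from-baseline contrast; adjust for baseline smoking and, in the same step, for the randomisation strata

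*Protocol article*

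**What the plan says.** All references are to the Methods of the protocol article.

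- **Randomization:** allocation is "on the class level within each school (group allocation is 1:1"), and "Different educational levels within 1 school grade are used for stratification". School and educational level are therefore design factors.
- **Outcomes:** "The primary end point is the difference of the change in smoking prevalence in the intervention group versus the difference in the control group", assessed at 12 months.
- **Analysis:** because "the group allocation is not on the individual level but on the class level", the model is "robust panel logistic regression (xtlogit procedure with vce [cluster] option"). For the primary end point: "This procedure is also used to calculate the difference from t1 to t3 of the smoking prevalence in the control group", set against the same difference in the intervention group.
- **Analysis, a separate sentence:** "The effects of predictors (gender, culture, and social characteristics) on smoking behavior after 12 months (t3") are to be estimated with the same type of model. This list concerns predictors of smoking. It is not a covariate list for the primary contrast.

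The form of the primary contrast is thus fixed in two places. The covariates in it are not listed: school, educational level and baseline smoking are neither named nor ruled out.

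**The concern.** In a randomised trial the expected baseline prevalence is the same in both arms. A difference in change and a baseline-adjusted difference at t3 therefore aim at the same intervention effect. The change contrast subtracts the whole baseline value, with its noise, whereas adjustment subtracts only the part that predicts follow-up. Unless t1 status predicts t3 status almost perfectly, or stable class differences are large, full subtraction costs precision.

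The trial has little to spare: Participants and Sample Size accepts 70% power and expects 18.6% loss to follow-up. Baseline status is measured anyway, and school and educational level are known from the randomisation.

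**Working it through.** **The plan's own figure.** The 70% power cannot be reproduced, because no effect size, ICC or number of classes is given. Taking the 5.9% public-school prevalence from the Introduction as the control value, 70% power would need a fall to about 3.2% (750 per arm, no clustering), 3.0% (1500 × 0.814 / 2 = 610 per arm, no clustering) or 1.8% (610 per arm, design effect 1 + 24 × 0.05 = 2.2). What follows is therefore relative precision only.

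**Inputs**
- Pupils per class at follow-up: m = 20, from about 25 per class (Overview of the intervention) × 0.814 = 20.4.
- Within-pupil correlation r, from 5.9% smokers at t1 and assumed quit and onset rates. The t1 variance is 0.059 × 0.941 = 0.0555.
  - Quit 0.35, onset 0.05: t3 prevalence 0.0854, variance 0.0781, covariance 0.0555 × 0.60 = 0.0333, so r = 0.51.
  - Quit 0.60, onset 0.04: t3 prevalence 0.0612, variance 0.0575, covariance 0.0555 × 0.36 = 0.0200, so r = 0.35.
- Class ICC c = 0.02, 0.03 or 0.05, assumed, with class effects that persist from t1 to t3.

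**Closed form** (equal variances of 1 at t1 and t3)
- Variance of a class mean: V = c + (1 − c)/m. Covariance of the t1 and t3 class means: C = c + (r − c)/m.
- Change: 2(V − C) = 2(1 − r)/m.
- Adjusted with pupil-level slope r: V(1 + r²) − 2rC.
- Adjusted/change = [(1 + r) + (m − 1)c(1 − r)]/2.

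| c | r = 0.35 | r = 0.51 |
|---|---|---|
| 0 (independent pupils) | 0.675 | 0.755 |
| 0.02 | (1.35 + 0.38 × 0.65)/2 = 0.80 | (1.51 + 0.38 × 0.49)/2 = 0.85 |
| 0.03 | (1.35 + 0.57 × 0.65)/2 = 0.86 | (1.51 + 0.57 × 0.49)/2 = 0.89 |
| 0.05 | 0.984 | 0.988 |

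The variance falls by about 10-20% at c = 0.02-0.03 and by 1-2% at c = 0.05. The ratio reaches 1 at c = 1/(m − 1) = 1/19 = 0.053; above that, under these assumptions, change is the more precise. Class effects that do not persist would give a larger gain.

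In power terms, if the change contrast had exactly 70% (1.960 + 0.524 = 2.484), the adjusted analysis would have Φ(2.484/√0.895 − 1.96) = 75% to Φ(2.484/√0.80 − 1.96) = 79%.

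**Simulation.** 60 classes in 10 strata, 20 retained pupils each, 1:1 within stratum, errors clustered on class, 400 runs per setting. Variance components and effects are assumed. Monte Carlo error is about ±5 points on power and ±2 on type I error.
- Pupil random-intercept logistic model, group × time, against the same model with a common baseline: power 55% against 69% (r about 0.22), and 69% against 81% (r about 0.47).
- Planned change contrast without strata: model SE/empirical SE 0.95-1.04, null rejection 4.8-6.5%. Adding strata to the pooled group × time model moved the SE by at most 2% (0.341 to 0.345; 0.341 to 0.348; 0.283 to 0.285) and power from 56.8% to 56.5% and from 73.0% to 73.0%.
- t3 model adjusted for baseline, without strata: SE up to 13% too large, null rejection down to 1.8%. The common-baseline panel model without strata behaved alike (14%, 1.5%).
- t3 model with baseline and strata: SE ratio 0.96 and 0.91 in two null settings, with 7.0% rejection in both. This is slightly liberal, though within simulation error of 5%.

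**The case against.** Difference-in-differences is unbiased under randomisation, matches the stated end point and uses baseline data as the t1 outcome. The panel logistic model works on the log-odds scale and does not analyse individual change scores. Preferring another valid estimator is a matter of efficiency, and the gain depends on variance components that the article does not give. All of this stands, and it sets the weight of the point. It does not remove it: the loss also appears in a simulation of the panel logistic form, and the contrast is something the article fixes, not a detail left to an analysis plan.

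Three stronger readings are tempting but not supported.

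- **The standard errors are wrong because the strata are left out.** Stable school and level differences largely cancel in a t1-to-t3 contrast, and the simulation shows almost no effect. The omission matters in a follow-up-only or common-baseline model, and there it errs on the conservative side. The article also addresses class clustering: "In order to take into account this clustering statistically we will use robust panel logistic regression".
- **The plan excludes the strata.** It gives no covariate list for the primary contrast, and a condensed article may leave that list to a fuller document. Only the absence of a mention can be stated.
- **Change is worse than ignoring baseline.** That can hold for independent pupils. With c = 0.02-0.03 and the correlations above, change has 6% (0.065/0.069) to 38% (0.0490/0.0785) lower variance than t3 alone.

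**Conclusion.** The point holds as one of efficiency and specification, not of validity. The planned contrast gives a sound test but usually spends more variance than it needs to. The size rests on assumptions: a variance about 10-20% lower for class ICC 0.02-0.03, 20 pupils per class and correlation 0.35-0.51; 12-14 power points in the simulated panel model; close to nothing at a persistent class ICC of 0.05, or when the within-pupil correlation is near 1. For a trial planned at 70% power the change should be made, but a result from the analysis as planned would not be invalid.

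**What to change.** Make the primary analysis t3 smoking status on group, adjusted for the pupil's t1 smoking status, school and grade/educational-level stratum, with standard errors clustered on the class as randomised. A panel model with a common baseline and the same strata terms is an equivalent choice. Pool strata that hold too few classes. State the clustering variable and use a small-sample correction for the number of classes, given the slightly liberal simulated rejection rates. Report the standardised prevalence difference, so that the result stays on the scale of the end point, and show raw change by arm descriptively. Align the end point wording in Outcomes with this analysis.

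Do not change the baseline handling alone: without the strata terms the new model would have standard errors that are too large.

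The cost is wording and code, plus a few degrees of freedom for the school and stratum terms. No new data are needed.

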### Participants and Sample Size

In accordance with the first evaluation of our program in Germany, a total of 1500 eligible secondary school students will be recruited [7]. Inclusion criteria are the attendance of grades 7-11 at public secondary schools in Brazil with age ranging from 12 to 17 years. Exclusion criteria are defined as inability to fulfill the inclusion criteria (ie, private schools, different grades). The age range for inclusion in the study is higher than in our German study [10] as the median age of smoking onset is higher in Brazil than in Germany [6,11]. As we expect the same loss-to-follow-up effect as in our quasi-experimental trial in Germany (18.6%), a test power of 70% and a 2-sided alpha of .05 are considered appropriate for our primary end point.

### Data Collection

A pencil-and-paper questionnaire is used for the collection of the data and the smoking status is biochemically validated by randomized CO measurements in the exhaled air of the students. In addition to sociodemographic data (age, gender, and school type), the questionnaire will capture the smoking status of the school students concerning cigarettes and multiple other tobacco products (such as e-cigarettes and water pipes). These items are based on 3 established studies [34-36] and were either used in the original form or adapted to the specific circumstances of this study.

The class teachers supervise their classes during the completion of the questionnaire and seal them right after completion for confidentiality reasons. The envelopes are then shipped to the Federal University of Ouro Preto in Brazil where they are opened and the data entry is performed.

### Biochemical Validation

Using a portable CO analyzer (Smokerlyzer piCO+, Bedfont Scientific Ltd), CO testing will be randomly performed at baseline and endline in at least 10% of students [37]. CO measurements will be supervised by medical students with recordings made in the afternoon. The cutoff point is defined as 6 parts per million or less for nonsmoking and more than 6 parts per million for smoking [38-40].

### Outcomes

The primary end point is the difference of the change in smoking prevalence in the intervention group versus the difference in the control group at 12 months of follow-up. The same longitudinal prevalence effects are studied on our females exclusively as a secondary outcome because our photoaging intervention is suspected to be more successful in females [41]. As our sample size is quite small, the secondary outcome criteria is met if 20% fewer females start smoking in the intervention group during the study period of 1 year. The differences in smoking behavior (smoking onset, quitting) between the 2 groups will be studied as additional secondary outcomes with a positive 20% difference in change of behavior set as met outcome criteria. A smoker is defined as a pupil who claims to smoke at least once in the past 30 days within the survey.

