**Methods:**

A randomized controlled trial will be conducted among approximately 1500 adolescents aged 12 to 17 years in grades 7-11 of public secondary schools in Brazil. The prospective experimental study design includes measurements at baseline and at 6 and 12 months postintervention. The study groups will consist of randomized classes receiving the standardized EAT intervention (90 minutes of mentoring in a classroom setting) and control classes within the same schools (no intervention). The questionnaire measures smoking status, gender, social, and cultural aspects as well as predictors of smoking. Biochemical validation of smoking status is conducted via random carbon monoxide measurements. The primary end point is the difference of the change in smoking prevalence in the intervention group versus the difference in the control group at 12 months of follow-up. The differences in smoking behavior (smoking onset, quitting) between the 2 groups as well as effects on the different genders will be studied as secondary outcomes.

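### The female secondary outcome is defined as change in smoking prevalence but judged on smoking onset, and a girls-only analysis cannot address its comparative rationale

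*Protocol article*

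**What the plan says.** In the protocol article, Methods, Outcomes, the primary end point is the between-arm difference in change of smoking prevalence at 12 months. The first secondary outcome follows directly: "The same longitudinal prevalence effects are studied on our females exclusively as a secondary outcome". The reason given is that "our photoaging intervention is suspected to be more successful in females".

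The next sentence says when this outcome counts as met: if "20% fewer females start smoking in the intervention group" over the one-year study period. The same paragraph then lists onset and quitting, compared between the two arms, as additional secondary outcomes with their own 20% criterion.

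The Abstract (Methods) describes the gender aim more widely: "effects on the different genders will be studied as secondary outcomes". The Conclusions of the Discussion also speak of measuring effects by gender. The Analysis section includes gender among the predictors of smoking behaviour at 12 months, in a logistic panel regression with cluster-robust errors. As written, that describes gender's association with smoking, not a difference between genders in the effect of the intervention.

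**The concern.** There are two separate faults in how the gender outcome is fixed.

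- **Definition and criterion do not match.** Prevalence at 12 months depends on how many non-smokers start and how many smokers stop. The criterion looks only at the first. The article itself treats onset as a different outcome, since it lists it as additional. A success on the criterion could sit beside unchanged or higher prevalence in girls, and a fall in prevalence achieved through quitting could sit beside a failed criterion.
- **Scope and rationale do not match.** More successful in females means more than in males. An estimate in girls alone carries no information on that comparison, and restricting the outcome to girls is narrower than the Abstract's description.

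At stake is the meaning of the first-named secondary outcome: whether a met criterion says anything about prevalence, and whether it says anything about gender.

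**Working it through.** **The plan's own figure.** The article gives no power or sample size for the female outcome. Its only power statement is that "a test power of 70% and a 2-sided alpha of .05 are considered appropriate for our primary end point". No effect size is given, so 70% cannot be reproduced, only back-solved. With 1500 x (1 - 0.186) = 1221 pupils retained, or about 610 per arm, 70% power requires roughly a halving of prevalence (5.9% to 3.0%), ignoring clustering. For girls alone, with about 305 per arm, a simple comparison of 12-month prevalence from 5.9% has power of about 10% at risk ratio (RR) 0.8, 28% at 0.6 and 43% at 0.5.

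**Inputs.** From the article: 1500 pupils, 18.6% loss, 1:1 allocation by class, and 5.9% smokers in public schools (Introduction; both genders together). Assumed: half the pupils are girls, girls also smoke at 5.9% at baseline, the 20% is relative (the article does not say), and there is no clustering. Onset and quit rates are assumptions too.

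- Girls per arm: 1221 / 4 = 305.
- Baseline non-smoking girls per arm: 305 x (1 - 0.059) = 287.

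**Check 1: can onset and prevalence disagree?** 12-month prevalence = 0.059 x (1 - quit rate) + 0.941 x onset. Control onset is 5%, so a 20% reduction gives 4%.

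| Case | Control | Intervention | Relative difference |
|---|---|---|---|
| Onset 20% lower, quitting 30% in both arms | 0.0413 + 0.04705 = 0.08835 | 0.0413 + 0.03764 = 0.07894 | 10.7% lower |
| Onset 20% lower, quitting 30% control, 10% intervention | 0.08835 | 0.0531 + 0.03764 = 0.09074 | 2.7% higher |
| Onset equal, quitting 10% control, 30% intervention | 0.0531 + 0.04705 = 0.10015 | 0.0413 + 0.04705 = 0.08835 | 11.8% lower |

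In the second case the criterion is met and prevalence rises. In the third, prevalence falls and the criterion is not met. The break-even in the first direction is 0.059 x (difference in quit rates) = 0.941 x 0.05 x 0.2 = 0.00941, a quit rate about 16 percentage points lower under intervention.

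**Check 2: what does a girls-only result say about gender?** As an illustration, the 20% rule was simulated with the same true effect in girls and boys (400,000 trials per scenario, 287 non-smokers per arm per gender, onset 3-8%).

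- True RR 0.8 in both genders: met in girls in about 51% of trials; met in girls but not boys in about 25% (0.51 x 0.49 = 0.25).
- No effect in either gender: met in girls in about 22-33%; met in girls but not boys in about 17-22% (0.224 x 0.776 = 0.17; 0.334 x 0.666 = 0.22).

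**Check 3: what would the interaction deliver?** Worked on onset, as the log ratio of the two risk ratios, with variance equal to the sum over the four arm-by-gender cells of 1/(287p) - 1/287. RR is 0.8 in girls and 1.0 in boys, so the difference is ln(1.25) = 0.223.

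- Control onset 8%: variance 0.0510 + 3 x 0.0401 = 0.171, SE 0.414, z = 0.54, two-sided power about 8%. The 95% limits are the estimate divided and multiplied by exp(1.96 x 0.414) = 2.25.
- Control onset 2%: variance 0.2143 + 3 x 0.1707 = 0.726, SE 0.852, z = 0.26, power about 6%. The factor is exp(1.96 x 0.852) = 5.3.
- With RR 0.6 in girls and 1.0 in boys, power is about 9-22% over the same onset range.

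The same calculation for prevalence change would also need the within-pupil correlation, which the article does not give.

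**The case against.** The strongest reply is that the article announces no test of girls against boys. The suspicion of greater success is the reason for prespecifying a subgroup, and estimating an effect where it is expected to be largest is a legitimate secondary outcome. That stands. A reader might infer that the plan will claim superiority in girls from a girls-only result; nothing in the article says so. What remains is that the stated reason is comparative, the chosen analysis cannot speak to it, and the Abstract describes a wider scope.

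Second, interaction terms and by-gender tables are commonly left to an analysis plan that is not shown here. That also stands, so their absence alone is not the point. But the restriction to girls exclusively is a stated choice, and the mismatch between definition and criterion stands in the published text. An added analysis would not remove either.

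Third, a reader might infer that onset has replaced prevalence for girls, or that the trialists may pick either after seeing the data. Neither follows. Prevalence in girls is still to be studied, and only one success criterion is stated.

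Fourth, the figures for girls but not boys apply a rule to boys that the plan does not set for them. For two equal independent groups they reduce to p(1 - p), and the reverse pattern is equally frequent. They reflect mainly a noisy rule stated without a test or interval. This is accepted: they illustrate why one gender's result is uninformative about the other, under assumed inputs, and do not measure an error rate of the plan.

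Last, the remedy cannot settle the gender question either. With power of 6-8% for the smaller contrast considered, that is correct.

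**Conclusion.** The point holds for a secondary outcome and should be corrected; the primary end point is untouched. The female outcome is defined on prevalence change and judged on onset, and the two can point in opposite directions: 20% less onset goes with prevalence 10.7% lower or 2.7% higher, depending on quitting. The directions are certain. The sizes rest on 5.9% baseline smoking in girls, 5% control onset and the quit rates chosen.

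The restriction to girls is narrower than the Abstract and cannot support its own comparative rationale. With an identical true RR of 0.8 in both genders, girls but not boys would meet the 20% rule in about a quarter of trials. This is an illustration assuming 50% girls, onset of 3-8%, a relative reading of 20% and no clustering. Clustering by class would change the simulated and power figures. The documents do not support the stronger reading that the trial plans to claim a female-specific effect.

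**What to change.** - In Outcomes, judge the female outcome on the same 12-month prevalence-change contrast as the primary end point. Keep onset, by gender if wanted, as a separate secondary outcome.
- Fit the clustered primary model to all pupils and let the intervention effect differ by gender. If the model carries baseline and 12-month records, the intervention effect is the group-by-time term, so the term needed is group by time by gender, with its lower-order terms.
- Report the effect with a 95% confidence interval in girls and in boys, plus the interaction contrast. Base any statement that the intervention works better in females on that contrast only.
- Use the same description of the gender outcome in the Abstract and in Outcomes.

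The cost is a few sentences and the extra model terms. Gender is already collected, so no new data are needed. The drawback is imprecision: on the onset scale the 95% limits for the ratio of risk ratios would lie a factor of about 2.25 to 5.3 either side of the estimate, under the assumptions above. It should be presented as an estimate, not as a powered test.

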## Introduction

Smoking is one of the main risk factors both for mortality and disability-adjusted life years (DALYs) for noncommunicable chronic diseases in Brazil and globally [1-3]. A study published in 2011 estimated the tobacco-related burden in Brazil and found that smoking was accountable in that year for 147,072 deaths and 2.69 million DALYs, representing a direct cost for the health system of $23.37 billion Brazilian real (US $7.37 billion) [4].

According to a large national study that was conducted in 2012 with 61,037 9th graders in Brazil, over 30.0% of 13- to 15-year-olds try smoking before the age of 12 (National School Health Survey—PeNSE) [5]. The newest data from the 2016 ERICA study with 74,589 Brazilian 12- to 17-year-old participants revealed a current smoking prevalence of 5.7% in this young age group with more smokers in public than in private schools (5.9% vs 4.4%) [6]. Although smoking rates among adolescents and emerging adults have substantially declined since the early 2000s, prevalence is still high and strong socioeconomic and educational inequalities in smoking exist in Brazil [6].

Founded in 2012 in Germany, Education Against Tobacco (EAT) has now enrolled participants in over 80 medical schools in 13 countries worldwide. The network has its roots in the school-based interventions delivered by medical students that cost about US $20 per participating class and reach up to 40,000 students per year worldwide. However, the network is also involved in medical education research on smoking cessation counseling, science-based multilanguage apps, and public awareness and advocacy for tobacco control [7-9].

The school-based intervention has only been evaluated for short-term effects with a quasi-experimental design with multiple potential sources of bias [10,11]. However, its preliminary evaluation involving 1474 students showed a significant reduction in the smoking prevalence of secondary school students in Germany at 6 months of follow-up after interventions motivating them to quit [10,11]. After this first evaluation, the curriculum was optimized for students with a lower educational level because the intervention was less effective in this subgroup [11]. This was done by making the program more interactive and by developing and involving a photoaging app (Smokerface) into our classroom intervention because published research suggests that there is effectiveness of photoaging strategies for our age group [7].

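### Secondary outcomes count as met at a 20% difference that is tied to no interval and, for onset and quitting, has no stated scale; read as relative, an ineffective programme would often pass

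*Protocol article*

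**What the plan says.** All the success rules for the secondary outcomes stand in the Outcomes section of the protocol article.

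- **Females.** The section opens the rule with "As our sample size is quite small" and continues: "the secondary outcome criteria is met if 20% fewer females start smoking in the intervention group during the study period of 1 year".
- **Onset and quitting, both sexes.** These are additional secondary outcomes, "with a positive 20% difference in change of behavior set as met outcome criteria". The small-sample reason is not repeated here.

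The Analysis section sets a 5% two-sided level for *t* tests and two-sided 95% confidence intervals. It notes that allocation is by class and names robust panel logistic regression with clustered standard errors. It names that model for predictor effects at 12 months and for the primary end point. It does not make a secondary criterion depend on the model or on an interval.

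Participants and Sample Size gives error rates for one outcome only: "a test power of 70% and a 2-sided alpha of .05 are considered appropriate for our primary end point".

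**The concern.** A threshold on the size of a difference, with no measure of its uncertainty, does not separate effect from chance. The fewer the events, the more easily a 20% difference arises from noise. A small sample is therefore a reason for caution about such a rule, not a reason to adopt it.

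The scale matters as well. For females, 20% fewer starters reads naturally as a relative reduction. For onset and quitting, a 20% difference could be relative or could mean percentage points. If the scale is not fixed before the data are seen, it can be chosen afterwards.

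The female outcome carries the hypothesis that photoaging works better in girls, and the Conclusions look to effects by gender to support the programme in Brazil. A secondary outcome reported as met would be read as evidence.

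**Working it through.** **The plan's own figure.** The article gives no false-positive rate or power for the secondary criteria, so there is nothing to reproduce. Its 70% power concerns the primary end point.

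**Inputs from the article**
- 1500 pupils, 1:1 allocation, 18.6% loss: 1500 × 0.814 = 1221 retained, about 610 per arm.
- 5.9% smoking prevalence in public schools (Introduction): 610 × 0.059 ≈ 36 baseline smokers and 610 × 0.941 ≈ 574 non-smokers per arm.

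**Assumptions not in the article**
- Half the pupils are female: 574 / 2 = 287 female non-smokers per arm.
- 12-month onset of 3-8%, also shown over 2-10%.
- Quit rate of 20-50%.
- No clustering at first, then a design effect of 1.5.

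**Formula, relative reading.** With X_I and X_C independent binomial counts with equal *n* and equal true rate, the chance that a null intervention passes is P(X_I ≤ 0.8 X_C) for onset and P(X_I ≥ 1.2 X_C) for quitting, summed exactly. Ties at zero do not count as a pass.

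| True onset, both arms | Female onset (287 per arm) | Overall onset (574 per arm) |
|---|---|---|
| 2% | 37% | 31% |
| 3% | 33% | 26% |
| 4% | 31% | 23% |
| 6% | 26% | 18% |
| 8% | 22% | 14% |
| 10% | 19% | 11% |

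| True quit rate, both arms | Quitting (36 per arm) |
|---|---|
| 20% | 36% |
| 30% | 32% |
| 40% | 27% |
| 50% | 23% |

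**Hand check, females at 6%.** Expected events per arm are 287 × 0.06 = 17.2. Under no effect the standard error of the log risk ratio is √[2 × (1/17.2 − 1/287)] ≈ 0.33. Then ln(0.8)/0.33 ≈ −0.68, a lower-tail probability of about 25%, against 26% exactly.

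**Clustering.** Dividing *n* by 1.5 raises most of these figures by about 3-5 points. Female onset at 6%, for example, goes from 26% to 30%.

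**What an observed 20% reduction tells us.** Females, 6% in control: 17.2 events against 0.8 × 17.2 = 13.8. The standard error is √(1/13.8 − 1/287 + 1/17.2 − 1/287) ≈ 0.35. The 95% interval is 0.80 × exp(±1.96 × 0.35), about 0.40 to 1.59 before clustering. A result that just meets the criterion is compatible with a large benefit and with a large harm.

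**Absolute reading, onset and quitting.** With 36 smokers per arm, a null intervention shows a gain of 20 points in quitting in about 1% of trials at a 20% quit rate and about 4% (3.8%) at 50%. For onset the probability is practically zero. With control onset of 3-8%, even zero onset under intervention gives a difference of only 3-8 points, so 20 points is out of reach.

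**The case against.** The strongest defence is that the article never says the 20% replaces testing. The female outcome is introduced as the primary prevalence effect restricted to girls. The Analysis section gives confidence intervals without limiting them to one outcome, and its remark on clustering covers the whole sample. The 20% could then be a relevance threshold beside that analysis. This is a condensed article, and detail on secondary models may stand elsewhere.

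Part of this stands. A reader might infer that the plan offers no interval and no allowance for clustering for these outcomes; the Analysis section does not support that. What remains is narrower: the Outcomes section states when a criterion is met, and the condition involves no interval. That is a rule set down in the text, not a detail left out.

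Other stronger readings also fail:
- That a null programme passes 14-36% of the time as a plain fact. The figures need the relative reading and rates the article does not give. At 15% onset they drop to about 14% for females and 6% overall, although such onset looks high beside a 5.9% prevalence.
- That the small sample is the stated reason for all three criteria. It is given for females only.
- That a true 20% effect being missed about half the time is a special fault. Any threshold set at the true value does that, and an interval-based rule would miss it more often.
- That the chance of meeting at least one of the three criteria is an error rate of the plan. The article makes no claim of success on any one of them.

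**Conclusion.** The point holds in a conditional form. The secondary success rules rest on a 20% difference that no test or interval supports, and for onset and quitting the scale is not stated.

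On the relative reading, with the assumptions listed above, a null intervention passes in about 22-33% of trials for female onset, 14-26% for overall onset and 23-36% for quitting, and somewhat more often with clustering. Over onset of 2-10% the two onset criteria span about 11-37%. On the percentage-point reading the problem reverses: quitting passes under the null in under 4% of trials, and the onset criterion could hardly be met by any programme. The same words thus allow a lenient rule or a nearly unattainable one.

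A reader might go further and infer that the trial's main conclusion is at risk. It is not: the primary end point has its own two-sided alpha of .05 and a class-clustered model, and the 20% rules do not touch it.

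**What to change.** In the Outcomes section, remove the 20% as the condition for a secondary outcome being met. For female onset, overall onset and quitting, state that:

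1. the effect is a risk ratio or risk difference among pupils at risk (baseline non-smokers for onset, baseline smokers for quitting);
2. it is reported with a two-sided 95% confidence interval that allows for clustering by class, following the approach already in the Analysis section;
3. an effect is claimed only if that interval excludes no difference;
4. 20% is kept, if wanted, only as a minimum relevant effect against which the interval is read, with its scale (relative or absolute) stated.

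The change is one of wording in Outcomes and Analysis and needs no new data. The cost is real, however. For a true relative reduction of 20% in female onset, at 6% against 4.8% with 287 per arm, the difference is 0.012 and its standard error √[(0.06 × 0.94 + 0.048 × 0.952)/287] ≈ 0.0189. The ratio is about 0.64, which gives power of about 10% at two-sided 5% before clustering. These outcomes would mostly be reported as estimates with wide intervals, and the text should say so in advance.
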